## Methods: participants, interventions, and outcomes

### Study setting {9}

This study will be a lab experiment conducted at Heidelberg University in Germany. Participants are college students who will be recruited through social media platforms, email lists, and flyers. During the preparation stage, an experimenter will guide the participant into an experiment room and instruct them to sit in front of a computer. For the main part of the experiment, the participant will independently follow instructions displayed on a computer screen administered via an online survey platform (Qualtrics, https://www.qualtrics.com/).

### Eligibility criteria {10}

The eligibility criteria for participants are:Participants must be full-time university students.Participants should be able to read English, as the entire experiment will be conducted in English.Participants must be aged 18–35 years old.To ensure a minimum level of computer literacy, participants must use the computer on most days of the week.To ensure that prior experience with the GRE would not confound the study results, participants must have NOT taken, or be preparing for, the GRE.To avoid issues with eye-tracking data collection, participants should not wear glasses or have any eye impairment (such as cranial nerve III palsy). For those who wear contact lenses, they should not be colored and should not exceed 300 degrees.Participants should not have any self-reported neurological or psychiatric disorders.

Participants who fulfill all eligibility criteria will be included in the study, while participants who do not fulfill the eligibility criteria will be excluded from the study.

Additionally, to participate in the study,Participants should withhold alcohol 24 h before participation. Otherwise, they will be excluded from the study.Participants should not wear makeup around the eyes, like mascara or eyeliner. If they do, they will be asked to wash it out before the experiment.

### Who will take informed consent? {26a}

Before the experiment starts, the participant will be given an information sheet and a consent form by the experimenter. The information sheet will explain the study’s aim, procedures, potential risks and benefits, compensation, and contact information of the study investigators. The experimenter will answer any questions that the participant may have before asking for consent. If the participant meets the inclusion criteria and agrees to participate, they will be asked to sign the consent form, which the experimenter will countersign. The participant will receive the information sheet and a copy of the consent form. The other copy of the consent form will be retained by the research team. All participants will be verbally informed that they can withdraw from the study at any time without giving any reason and without having any negative consequences to their academic studies.

### Additional consent provisions for collection and use of participant data and biological specimens {26b}

Not applicable. No data will be collected for ancillary studies.

## Interventions

### Intervention description {11a}

In the intervention group, the computer screen will be set up in a split-screen format. On the left side of the screen, the participant will receive instructions on the writing prompt, writing requirements, time requirements, grading feedback, and the grading rubric. The instructions will also highlight to the participant that they can use ChatGPT in any way they like to assist their writing, and there is no penalty in their writing score for how ChatGPT is used. The right side of the screen will display a blank ChatGPT interface where the participant can prompt questions and receive answers.

### Explanation for the choice of comparators {6b}

In the control group, as in the intervention group, the computer screen will be set up in a split-screen format. On the left side of the screen, the participant will receive the same instructions on the writing prompt, writing requirements, time requirements, grading feedback, and the grading rubric. Additionally, the instructions will highlight to the participant that they can use a text editor in any way they like to assist their writing. On the right side, instead of ChatGPT, a basic text editor interface will be displayed. In summary, this comparator will keep the split-screen format consistent between the two groups and ensure that participants in the control group will complete the writing task with minimal support.

### Criteria for discontinuing or modifying allocated interventions {11b}

This study is of minimal risk, and we do not anticipate needing to discontinue or modify the allocated interventions during the experiment. Participants can withdraw from the study at any time.

### Strategies to improve adherence to interventions {11c}

Adherence to the interventions will be high because the procedures are straightforward and will be clearly explained in the step-by-step instructions on the computer screen. The participant will be alone in a noise-canceling room during the entire experiment. The participant can reach out to the experimenter through an intercom if they need any clarification.

### Relevant concomitant care permitted or prohibited during the trial {11d}

Not applicable. This is not a clinical study.

### Provisions for post-trial care {30}

Not applicable. This is a minimal-risk study.

### Outcomes {12}

The study has two primary outcomes. First, we will measure participants’ writing performance scores on the analytical writing task. The task is adapted from the Analytical Writing section in the GRE, a worldwide standardized computer-based exam developed by the Educational Testing Service (ETS) [27]. Participants’ writing performance will be scored using the GRE 0–6 rubric and by an automatic essay-scoring platform called *ScoreItNow!*, which is powered by ETS’s e-rater engine [32, 33]. We chose to adapt from the GRE writing materials for two reasons. First, their writing task and grading rubrics were established writing materials designed to measure critical thinking and analytical writing skills and have been used in research as practice materials for writing (e.g. [34]). Second, OpenAI’s technical report shows that ChatGPT (GPT-4) can score 4 out of 6 (~ 54th percentile) on the GRE analytical writing task [31]. This gives us a benchmark for assessing the potential increase in writing performance when individuals collaborate with generative AI.

Second, we will measure participants’ cognitive effort during the writing process. Participants’ cognitive effort will be measured using a psychophysiological proxy—i.e., changes in pupil size [35, 36]. Pupil diameter and gaze data will be collected using the Tobii Pro Fusion eye tracker at a sampling rate of 120 Hz. During the preparation stage of the study, the room light will be adjusted so that the illuminance at the participants’ eyes is at a constant value of 320 LUX. Baseline pupil diameters will be recorded during a resting task in the experiment preparation stage that asks the participant to stare at a cross that will appear for 10 s each on the left, center, and right sections of the computer screen. Pupil diameters and gaze data will be recorded throughout the writing process.

The study has several secondary outcomes. First, to identify the neural substrates of cognitive effort during the writing process, we developed an additional psychophysiological proxy, changes in the cortical hemodynamic activity in the frontal lobe of the brain. Specifically, we will examine hemodynamic changes in oxyhemoglobin (HbO). Brain activity will be recorded throughout the writing process using the NIRSport 2 fNIRS device and the Aurora software with a predefined montage (Fig. 2). The montage consists of eight sources, eight detectors, and eight short-distance detectors. The 18 long-distance channels (source-detector distance of 30 mm) and eight short-distance channels (source-detector distance of 8 mm) are located over the prefrontal cortex (PFC) and supplementary motor area (SMA) (Fig. 2). The PFC is often involved in executive function (e.g., cognitive control, cognitive efforts, inhibition) [37, 38]. The SMA is associated with cognitive effort [39, 40]. The sampling rate of the fNIRS is 10.2 Hz. Available fNIRS cap sizes are 54 cm, 56 cm, and 58 cm. The cap size selected will always be rounded down to the nearest available size based on the participant’s head measurement. The cap is placed on the center of the participant’s head based on the Cz point from the 10–20 system.

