Within the third stage, the participant will first complete a pre-survey. They will then be instructed to read some materials to learn about analytical writing, and then practice what they have learned by writing an analytical essay as their homework assignment. During practice, the instructions will outline the writing prompt, writing requirement, time requirement, grading feedback, and grading rubric. Specifically, the participant will be asked to write a 350–600-word essay stating whether they agree or disagree with the writing prompt. The time requirement will explain that there is no time limit, but participants are recommended to spend 30 min on the task. We intentionally designed the writing task without a time limit to better reflect a typical homework setting, in contrast to an exam setting where time is constrained. This distinction may elicit different writing behaviors and patterns of using AI tools. For grading feedback, the instructions will explain that the participant will receive their writing score, the class average, and writing feedback from expert instructors once the entire experiment ends. Participants in the intervention group can use ChatGPT to support their writing. Specifically, we choose GPT-4 because it has been independently benchmarked for its standalone performance on analytical writing in the Graduate Record Examinations (GRE), as documented in OpenAI’s technical report [31]. This provides a reference point for us to evaluate the analytical writing capabilities during human-generative AI collaboration. Participants in the control group will complete the writing task without AI assistance. After the writing task, the participant will complete a post-survey. The entire study will last for approximately 1.5 h for each participant.

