## Statistical methods

### Statistical methods for primary and secondary outcomes {20a}

Here, the intervention effect on the two primary outcomes will be estimated by an intent-to-treat analysis. Our first primary outcome, writing performance, will be treated as a continuous variable. Our second primary outcome, cognitive effort as measured by mean changes in pupil size, will also be treated as a continuous variable. We will estimate the intervention effect on each outcome separately using ordinary least squares (OLS) regression with heteroskedasticity-robust standard errors. To control for type I error inflation due to multiple testing, we will apply a Bonferroni correction. Accordingly, the adjusted significance threshold is set at *α* = 0.05/2 = 0.025. The outcome of cognitive effort is a psychophysiological measure recorded throughout the entire writing process. Standard pre-processing steps will be taken before the statistical analysis [51, 52], such as correcting for screen angle distortion, removing invalid data that do not reflect the actual pupil size (pupil size below 1.5 mm or over 9 mm [53], often due to blinking), smoothing to remove small oscillatory and noise activity, interpolating blink related invalid data, downsampling, and correcting pupil size changes based on the baseline pupil size that will be collected during a 30-s relaxation task at the beginning of the experiment. Participant-level data will be excluded if the data do not meet basic quality standards, such as having a high proportion of invalid data.

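### The co-primary pupil contrast compares arms that look at different right-hand panels, and the protocol describes no matching or measurement of task-screen luminance.

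*Protocol article*

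**What the plan says.** Statistical methods {20a} defines the second primary outcome as "cognitive effort as measured by mean changes in pupil size, will also be treated as a continuous variable", compared between arms by OLS at a Bonferroni threshold of 0.025. Outcomes {12} gives the recording period: "Pupil diameters and gaze data will be recorded throughout the writing process".

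The screens differ by arm. Intervention description {11a}: "The right side of the screen will display a blank ChatGPT interface". Explanation for the choice of comparators {6b}: "On the right side, instead of ChatGPT, a basic text editor interface will be displayed". The left-hand instructions cover the same items in both arms, except for the line on which tool may be used. The claim of comparability is that "this comparator will keep the split-screen format consistent between the two groups".

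On light, Outcomes {12} states: "During the preparation stage of the study, the room light will be adjusted so that the illuminance" at the participant's eyes is held at 320 lux. The baseline is a rest task with a fixation cross shown for 10 s at each of three screen positions, also during preparation. Section {20a} lists pre-processing steps by way of example, including correction to this baseline. The covariates named there are three self-reported skills and motivation, plus other baseline measures found to differ between arms.

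Task length is self-chosen. Trial design {8} says "there is no time limit, but participants are recommended to spend 30 min on the task".

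**The concern.** Pupil size responds to light as well as to effort. The protocol accepts this, since it standardises illuminance at the eye. The one optical factor that is tied to the arm by design is the task display, and for that factor no matching and no measurement is described.

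A luminance difference between the panels would be a systematic offset carried by assignment. It would not average out over participants, and a larger sample would only make it more likely to reach significance. It could imitate an effect on effort or hide a real one. The trial aims to establish a causal effect on cognitive effort, and the Discussion rests internal validity on the controlled lab setting, so the gap touches a central claim.

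**Working it through.** **Step 1. What each safeguard removes.** Let *e* be the effort-related pupil change, *b* the participant's own level, *L*(arm) the light-driven component on the task screen and *L*(rest) that on the rest screen. Assume that these add.

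- Task pupil size = *b* + *e* + *L*(arm).
- Baseline pupil size = *b* + *L*(rest).
- Baseline-corrected change = *e* + *L*(arm) − *L*(rest).
- Difference between arms = [*e*(ChatGPT) − *e*(control)] + [*L*(ChatGPT) − *L*(control)].

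Subtracting the baseline removes *b*, and *L*(rest) cancels between arms. The second bracket stays. Randomization balances *b* but not the second bracket, because the panel comes with the assigned arm. Skill, motivation and baseline characteristics do not measure it either. It is zero only if the panels are equally bright where participants look, or if it is measured and corrected.

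**Step 2. The plan's own figure.** The only sample size stated is 160, for writing performance (d = 0.45, SD 1, alpha 0.05, power above 0.8). The normal formula gives n per arm = 2(1.960 + 0.842)²/0.45² = 77.5, so 78, or 156 in total. The noncentral-t version gives 79 per arm, or 158. With 80 per arm, power is 0.808. The figure of 160 reproduces, so this point does not rest on a sample-size error. No size calculation is given for the pupil outcome.

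**Step 3. Illustration of an offset.** Inputs from the protocol: 80 per arm (160 at 1:1) and alpha 0.025. Two-sided testing is assumed. The protocol gives no pupil SD and no luminance, so the offset δ, in SD units, is an assumption shown over a range. With no difference in effort, the rejection probability comes from the noncentral t with 158 degrees of freedom and noncentrality δ√(80/2) = 6.325δ.

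| Assumed offset (SD) | Noncentrality | Probability of a significant result |
|---|---|---|
| 0 | 0 | 2.5% |
| 0.1 | 0.63 | 5.5% |
| 0.2 | 1.26 | 16% |
| 0.3 | 1.90 | 36% |
| 0.5 | 3.16 | 82% |

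In millimetres, an assumed offset of 0.10 mm gives 82%, 44% or 25% for an assumed SD of 0.2, 0.3 or 0.4 mm.

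**Step 4. Task length.** A mean does not grow with duration. Length affects it only through drift over time or a changed mix of activities. With an assumed linear drift of D SD per 30 minutes, the mean over T minutes shifts by D·T/60. An assumed 15 against 30 minutes then differs by D/4: 0.075 SD for D = 0.3 and 0.25 SD for D = 1.0. These give rejection in 4.2% and 25% of trials. Only substantial drift matters, so this is secondary to the luminance question.

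**The case against.** The strongest reply is that no bias has been shown. The protocol does not say that the two panels differ in brightness; both could have the same background. The layout is common to both arms, only the right half differs, and room light of 320 lux limits what half a screen can contribute. The percentages above are power arithmetic on assumed shifts. All of this stands, and it is why the size must be left open.

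Three further inferences are tempting, and the text does not support them. A reader might conclude that the light was set with the resting cross on screen; the protocol does not say what was displayed then. A reader might conclude that light is uncontrolled during writing; the 320 lux is described as constant, although no check or log during the task is mentioned. A reader might conclude that no luminance correction will be made; the pre-processing steps are given as examples and gaze is recorded, so a correction is not excluded.

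fNIRS and self-rated effort measure the same construct without relying on pupil size, and the Discussion plans to compare sources. They can corroborate a finding, but they are secondary and do not repair the pupil contrast itself.

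On duration, a reader might infer that a whole-task mean cannot answer the trial's question because it ignores time spent. The Background defines effort as the extent to which mental resources are used while the task is performed, which an intensity measure fits. The absence of a time limit is deliberate and explained, and a difference in duration is partly an effect of the intervention. Dilation integrated over time would be a different quantity, not a correction. The exploratory sub-task analyses in {20b} also address part of the concern about phases of work.

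**Conclusion.** The point holds as a gap in the described data collection for a co-primary outcome. The arms see different right-hand panels, the described light setting and the baseline both belong to the preparation stage, and nothing described would remove a luminance offset between panels if one exists. Whether one exists, and how large it is, cannot be told from the protocol. The 16%, 36% and 82% are conditional on assumed offsets of 0.2, 0.3 and 0.5 SD, two-sided testing and 80 analysed per arm; they show sensitivity, not an expected error rate.

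This is not a detail to leave to an analysis plan: panel appearance and light readings are fixed when data are collected, and unmatched screens cannot be matched afterwards. The whole-task mean remains a sound primary measure. Self-chosen task length justifies optional supporting results and no more.

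**What to change.** In {6b} and {12}:

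- State that both right-hand panels use the same theme, background colour and display brightness.
- Set the 320 lux with the participant's task screen displayed, and log the reading for each session.
- Record the resting baseline on the same background as the task screen.

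The cost is a display setting and one light reading per session, with a slightly longer set-up. Under {17a} experimenters already configure the screen by arm, so no new role is needed.

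Optionally, report writing time by arm, and add as a sensitivity analysis the mean pupil change over a common initial window that nearly all participants reach. Both use data from the planned sessions. Keep the whole-task mean as the primary measure.

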**Fig. 2 Fig2:**
[figure not shown]
Design of the fNIRS montage

Third, we will measure participants’ subjective perceptions of the writing task by self-reported survey measures in the post-survey (Table 1). We will measure participants’ subjective perceptions of the two primary outcomes—that is, their self-perceived writing performance and self-perceived cognitive effort. Self-perceived writing performance will be measured with a one-item scale using the same grading rubric described in the instructions for their writing task and used in the scoring tool. Self-perceived cognitive effort will be measured using a one-item scale adapted from the National Aeronautics and Space Administration-task load index (NASA-TLX) [41, 42]. We will also measure participants’ subjective perceptions of several mental health and learning-related outcomes, including stress, challenge, and self-efficacy in writing. Self-perceived stress will be measured using a one-item scale adapted from the Primary Appraisal Secondary Appraisal scale (PASA) [43, 44]. Self-perceived challenge will be measured using a one-item sub-scale adapted from the Primary Appraisal Secondary Appraisal scale (PASA) [43, 44]. Self-efficacy in writing will be measured using a 16-item scale that measures three dimensions of writing self-efficacy: ideation, convention, and self-regulation [45]. Furthermore, we will measure participants’ situational interest in analytical writing using a four-item Likert scale adapted from the situational interest scale [46]. Additionally, we will measure participants’ behavioral intention to use ChatGPT in the future for essay writing tasks [47].

**Table 1 Tab1:** Scales in the post-survey

Construct	Items	Response
Self-perceived writing performance	Using the same grading rubric from before, what score do you think your essay should get (0 being the lowest and 6 being the highest)?	0 to 6 scale
Self-perceived cognitive effort	On a scale of 1 to 7, rate how hard you had to work to accomplish your level of performance	1 to 7 scale
Self-perceived stress	On a scale of 1 to 7, how much would you agree or disagree with the following statement on perceived stress: The analytical writing assignment was stressful to me	1 to 7 Likert scale, 1 being “strongly disagree” and 7 being “strongly agree”
Self-perceived challenge	On a scale of 1 to 7, how much would you agree or disagree with the following statement on perceived challenge: I find the analytical writing assignment a challenge	1 to 7 Likert scale, 1 being “strongly disagree” and 7 being “strongly agree”
Self-efficacy in writing—ideation	On a scale of 1 to 7, how much would you agree or disagree with the following statements on coming up with ideas during your writing? 1. I could think of many ideas for my writing 2. I could put my ideas into writing 3. I could think of many words to describe my ideas 4. I could think of a lot of original ideas 5. I knew exactly where to place my ideas in my writing	1 to 7 Likert scale, 1 being “strongly disagree” and 7 being “strongly agree”
Self-efficacy in writing—convention	On a scale of 1 to 7, how much would you agree or disagree with the following statements on writing the essay properly? 1. I could spell my words correctly 2. I could write complete sentences 3. I could punctuate my sentences correctly 4. I could write grammatically correct sentences 5. I could begin my paragraphs in the right spots	1 to 7 Likert scale, 1 being “strongly disagree” and 7 being “strongly agree”
Self-efficacy in writing—self-regulation	On a scale of 1 to 7, how much would you agree or disagree with the following statements on regulating yourself during writing? 1. I could focus on my writing for the whole time 2. I could avoid distractions while I wrote 3. I could start the essay quickly 4. I could control my frustration when I wrote 5. I could think of my writing goals before I wrote 6. I could keep writing even when it was difficult	1 to 7 Likert scale, 1 being “strongly disagree” and 7 being “strongly agree”
Situational interest in analytical writing	On a scale of 1 to 7, how much would you agree or disagree with the following statements on your interest in the analytical writing assignment that you just completed? 1. The analytical writing assignment was interesting 2. Working on the essay was fun 3. I enjoyed writing the essay 4. The analytical writing assignment was enjoyable	1 to 7 Likert scale, 1 being “strongly disagree” and 7 being “strongly agree”
Behavioral intention to use ChatGPT in the future for essay writing tasks	On a scale of 1 to 7, how much would you agree or disagree with the following statements on using ChatGPT in essay writing assignments? 1. If I have access to ChatGPT, I would use it for essay writing tasks 2. I plan to use ChatGPT in the future if I have an essay writing task	1 to 7 Likert scale, 1 being “strongly disagree” and 7 being “strongly agree”

